##### Feasibility: Attrition and Adherence

We will collect data about the feasibility of the treatment in the form of weekly use data (Calm Place group) and study attrition and adherence to treatment (VR-CBT group). These metrics will be assessed by the number of treatment sessions attended, completion of treatment, percentage of sessions attended, number of patients who dropped out, and when possible, reasons for dropping out, comments and notes on feasibility in diary responses, the time spent using the program, and consistency in using the program over 10 weeks. Treatment completers for VR-CBT will be defined as individuals who attend 7 out of 10 sessions, and for Calm Place, 7 reported sessions over 10 weeks. Dropouts for VR-CBT are defined as individuals missing 2 consecutive sessions of therapy without rescheduling (no-show). Noncompleters are individuals who complete <7 sessions (but attend at least 1). In the case participants are judged by the research team as *at risk* (eg, psychologically), they may also be withdrawn from the study.

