##### Calm Place as the Active Control

During the use of the VR application, the Calm Place user may see flowing water, mountains, and tree cover; a tropical atoll with sand, palm trees, and the ocean; or an arctic scene with large pines, snow cover, and large stones. In Calm Place, each virtual environment offers applications [25,28], such as visual breathing aids, time and weather cycles, and meditation voice overs, with the guidance of the VR program. Here, the guidance on relaxation is nonpersonalized and is based on the selections of the user within the VR environment. Thus, though participants’ weekly choices regarding prevalence and duration of use are self-managed and done from their home, this intervention involves guided programming for guidance. The self-management program—Calm Place—does not have any avatar, social-interactive, or personalized components. The research team will contact these minimal-attention control participants weekly to check whether they use the application and to verify their safety.

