##### Week 10 to 11: Repeat Measure of Subjective and Objective Measurements

Once the intervention is complete, participants repeat the questionnaires and the reactivity testing paradigm from week zero to provide a second measurement.

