### Objective Measures

The participants will undergo a psychophysiological reactivity testing paradigm. This will be repeated after the end of the VR intervention for those who completed a minimum of 7 and a maximum of 10 sessions of therapy as soon as possible after the final session. We will collect and measure several metrics, including heart rate, blood volume pulse, skin conductance, blood pressure, and accelerometer data. Participants first respond to baseline subjective arousal, emotional arousal, and VAS-EV. We then begin collecting psychophysiological data with a portable finger sensor, covered with a piece of cloth for light sensitivity, by attaching it to the participant’s nondominant index finger. They fill out a survey, including several symptom scales as described during this approximately 15-minute period, and have their blood pressure taken with an ambulatory blood pressure machine. We also record a no-task seated baseline recording of sensor data for 3 minutes. Then, participants will familiarize themselves with VR in a forest walk environment with no tasks other than to walk and explore (5.5 minutes), with minimal interaction with the research team. In the next segment, participants walk a VR plank exposing them to the heights below for 5.5 minutes (instructed to walk back and forth, with no interaction). If the exercise is too challenging (eg, participant distress at a tolerable level), participants remain in the environment without walking for 2 minutes or withdraw completely (eg, intolerable distress) from the exercise. Finally, participants re-enter the same VR environment, this time with a floor rather than a plank beneath them and walk (3 minutes). The last segment is a 10-minute seated rest period. After each segment, participants report using the same visual analog scales.

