### Conclusions

The proposed study responds to the community’s desire for accessible and appropriate resources for psychological well-being, as it was developed in active collaboration with the Inuit community in Québec. We will observe preference for therapist-guided, at-clinic treatment, or at-home self-management and compare the acceptance and feasibility of a culturally adapted, VR-assisted psychotherapy with a commercial self-management program in VR. We incorporate novel technology in providing treatment and in objective outcome measurement in the area of Indigenous health. We also aim to fulfill the needs for RCTs to test the efficacy of culturally adapted psychotherapies.

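### Completion is counted differently in the two arms, the VR-CBT completer and dropout groups overlap, and the same 7-session threshold limits who is retested on a primary outcome

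*Protocol article*

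**What the plan says.** *Feasibility: Attrition and Adherence* sets the completer rule for both arms: participants who "attend 7 out of 10 sessions, and for Calm Place, 7 reported sessions over 10 weeks". It adds two further categories: "Dropouts for VR-CBT are defined as individuals missing 2 consecutive sessions of therapy without rescheduling (no-show", and "Noncompleters are individuals who complete <7 sessions (but attend at least 1". No order of precedence is given between completer and dropout.

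*Calm Place as the Active Control* says that participants' "weekly choices regarding prevalence and duration of use are self-managed and done from their home", and that the team "will contact these minimal-attention control participants weekly to check whether they use the application".

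The same threshold reappears under *Objective Measures*, where the post-treatment reactivity test is repeated "for those who completed a minimum of 7 and a maximum of 10 sessions of therapy as soon as possible after the final session". *Week 10 to 11: Repeat Measure of Subjective and Objective Measurements* says that, after the intervention, "participants repeat the questionnaires and the reactivity testing paradigm from week zero", with no session minimum.

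The comparison is intended. *Research Aims* makes feasibility versus the self-management program a primary aim, and *Conclusions* says the study will "compare the acceptance and feasibility of a culturally adapted, VR-assisted psychotherapy with a commercial self-management program in VR".

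**The concern.** In VR-CBT the count cannot exceed ten, and seven of those ten occasions must be used. In Calm Place the count has no ceiling, and no spacing, minimum length or weekly limit. Seven short uses in the first week would make a completer. Two arms with the same week-to-week engagement could then show different completion rates because of the counting rule alone. *Strengths and Limitations* suggests that a therapist-guided, culturally adapted treatment could improve attendance; a more lenient control-arm rule would hide that difference.

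The overlap means that completers and dropouts in VR-CBT need not be separate groups, so their counts cannot be read as parts of a whole.

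The retest restriction has a different consequence. The Abstract and the *Measures* section place the reactivity paradigm with the primary outcome. Limiting its second measurement to people who reached 7 sessions selects on behaviour after randomisation that the assigned arm can influence, so the between-arm comparison is no longer protected by randomisation.

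**Working it through.** The protocol gives no figure computed from these definitions, so there is nothing to reproduce. The rates below are illustrations.

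**Inputs from the protocol:** 10 sessions, 10 weeks, threshold 7, 20 per arm, two consecutive no-shows for dropout.

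**Assumptions (not in the protocol):** one VR-CBT session per week, independent weeks, and no rescheduling. The weekly probability *a* of attending (VR-CBT) or of using the program at all (Calm Place) is the same in both arms. Write *m* = 1 − *a*, and let *f* be the share of active Calm Place weeks with two uses instead of one.

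**1. Completion under each rule**

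- VR-CBT, participants may resume after no-shows: P(Bin(10, *a*) ≥ 7).
- Calm Place, every use counts: Σₖ P(Bin(10, *a*) = k) × P(Bin(k, *f*) ≥ 7 − k), where k is the number of active weeks.

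At *a* = 0.7, P(k = 4, 5, 6) = 0.0368, 0.1029, 0.2001 and P(k ≥ 7) = 0.6496.

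- *f* = 0: 0.650, identical to VR-CBT.
- *f* = 0.25: 0.0368 × 0.0508 + 0.1029 × 0.3672 + 0.2001 × 0.8220 + 0.6496 = 0.854.
- *f* = 0.50: 0.0368 × 0.3125 + 0.1029 × 0.8125 + 0.2001 × 0.9844 + 0.6496 = 0.942.

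| *a* | VR-CBT rule | Calm Place, *f* = 0 | *f* = 0.25 | *f* = 0.50 |
|---|---|---|---|---|
| 0.7 | 0.650 | 0.650 | 0.854 | 0.942 |
| 0.8 | 0.879 | 0.879 | 0.962 | 0.989 |
| 0.9 | 0.987 | 0.987 | 0.997 | 0.999 |

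At *a* = 0.7 and *f* = 0.25 the gap is 0.854 − 0.650 = 0.204, about 4 of 20 participants, with identical engagement.

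**2. Completer and dropout at once (VR-CBT)**

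The protocol does not say whether two no-shows end therapy, so both cases are needed. They exclude each other, and figures from one must not be combined with figures from the other.

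- *Two no-shows end therapy.* The overlapping patterns are: sessions 1–7 attended and 8–9 missed; 1–8 attended and 9–10 missed; or one isolated miss among the first seven sessions, with 7 attended by session 8 and 9–10 missed. Probability: *a*⁷*m*² + *a*⁸*m*² + 7*a*⁷*m*³ = 0.028, 0.027, 0.012 at *a* = 0.7, 0.8, 0.9.
- *Participants may resume, and every miss is a no-show.* Two consecutive misses occur in 64 of the 120 patterns with exactly 7 attended, in 9 of the 45 with exactly 8, and in none with 9 or 10. Probability: 64*a*⁷*m*³ + 9*a*⁸*m*² = 0.189, 0.168, 0.069. This is an upper value, because rescheduled misses do not count.

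The choice also changes completion. If two no-shows end therapy, completion at *a* = 0.7 is 0.461 (7 or more attended, no consecutive misses) + 0.028 = 0.489, not 0.650.

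**3. Who is retested**

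Set side by side, *Objective Measures* requires 7 to 10 therapy sessions and *Week 10 to 11* requires none. If the 7-session threshold is applied with each arm's own count at *a* = 0.7, the retested share is 49–65% in VR-CBT (10–13 of 20) and 65–94% in Calm Place (13–19 of 20, for *f* from 0 to 0.50). Those left out number 7–10 and 1–7.

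**The case against.** **A condensed article may leave counting rules to the full protocol or the analysis plan.** This would answer a missing rule. Here the article states the rules, and as stated they are not comparable and not mutually exclusive. The objection does stand for dropout in Calm Place. A reader might infer that the absence of a dropout rule in that arm is itself an error. The text does not support that: the section assigns attrition and adherence to VR-CBT and weekly use data to Calm Place, and a matching rule is an optional detail.

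**Seven reports over ten weeks may mean one report per week.** The weekly contact and the weekly use data make this reading possible, and under it the gap is zero. The text does not state it, and the self-chosen frequency points the other way. A reader might infer that a sizeable artificial gap is certain; it is not, because its size depends on multiple use within weeks, about which the protocol gives no information.

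**Other measures would reveal bunched use.** Time spent, consistency over ten weeks and percentage of sessions attended are also collected. That limits the damage, but none of them enters the completer definition. The protocol also sets no formal test or go/no-go threshold on completion.

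**The two retest statements can be reconciled.** The week 10–11 section speaks of the intervention being complete, which might mean completers only. But the same sentence covers the questionnaires, and the rating-scale analysis states no such restriction. Calm Place does have reported sessions, so the threshold could be carried over; still, sessions of therapy with a maximum of ten describe self-managed use poorly.

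**Conclusion.** The point holds in three parts.

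- **Completion** is not comparable between the arms as written. The difference due to counting alone runs from none (one count per week) to about 20–29 percentage points at 70% engagement, if a quarter to a half of active weeks hold two uses. It falls to about 1 point at 90% engagement.
- **The VR-CBT categories overlap.** This follows from the wording without any assumption; only its frequency is assumed. At 70–90% attendance it is 1–3% of participants if two no-shows end therapy, and at most 7–19% if they may resume.
- **Eligibility for the reactivity retest** is stated in two conflicting ways, and the restrictive one selects a primary outcome on adherence after randomisation.

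All percentages rest on assumed engagement, independent weeks and weekly sessions. A reader might infer that the DERS-16 comparison is compromised too. The documents do not support this: *Analyses for Rating Scales* applies no completer restriction to it.

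**What to change.** 1. In *Feasibility: Attrition and Adherence*, define a Calm Place completer as a participant with reported use at 7 or more of the 10 weekly contacts, and report the raw number of uses beside it.
2. In the same section, count VR-CBT dropouts only among participants with fewer than 7 sessions attended. The overlap then becomes zero.
3. In *Objective Measures*, offer the week 10–11 reactivity retest to all randomised participants in both arms, in line with the week 10–11 section.

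**Cost.** The first two changes are wording only, since weekly contacts and weekly use data are already planned. Fewer Calm Place participants may then count as completers. The third adds one-hour tests: at 70% engagement about 7–10 in VR-CBT (20 × 0.35 to 20 × 0.51) and about 1–7 in Calm Place (20 × 0.06 to 20 × 0.35). That is 8–17 in total, or about CAD 120–255 at the stated CAD 15 per hour, plus staff time. Some of those invited will decline.

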#### Randomization and Masking

After receiving informed consent for participation, a research assistant will use a computerized randomization generator to randomly assign participants in a simple 1:1 ratio (VR-CBT or Calm Place). Before randomization, we will show participants the treatment rationales, explaining the 2 possible study groups. They will report their preference for either treatment in a forced-choice question, rate their preference for each treatment on a scale from 1 to 10, and provide comments on why they selected this choice. This information is collected to inform future larger trials and clinical services. The treatment cannot be supplied blinded to the content. However, as the measurements are self-reports and objective measurements, we do not use blinded outcome evaluation. Once random assignments are decided, they will be kept hidden from researchers and research assistants until the participants begin the trial.

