##### Weeks 1 to 10: Intervention Period and Weekly Questionnaires

During the intervention period, we will send participants biweekly questionnaires. In their final visit, participants will repeat the procedures from the first visits (visits 1 and 2). Participants will receive a small financial compensation (gift card) for each visit.

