##### Week 22: Postintervention Follow-up

Twelve weeks after their final visit, we will follow up with the participants on all baseline questionnaires.

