### Data Analysis

#### Analyses for Rating Scales

Expecting nonnormally distributed data in a small human sample, we will conduct nonparametric tests and generate descriptive and comparative statistics to detect between-group differences for the 2 conditions, VR-CBT (A) and Active Control VR program (B), using R Statistical and Computing Software (R Core Team). We will use generalized mixed linear models to compare the 2 conditions using scores on DERS-16 across several time points (pre- and posttreatment as well as biweekly and bimonthly time points). In addition, we will describe changes in mood, anxiety, and trauma symptoms for the 2 conditions (pre- and posttreatment, as well as biweekly and bimonthly time points). The data collection for time points varies based on the administration instructions for each scale (weekly, biweekly, monthly, etc). Cohen *d* or nonparametric tests will calculate the effect size between the 2 conditions.

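### The at-risk rule withdraws participants from the study and not only from the intervention, so later outcomes that are plausibly informative may go uncollected (cheap improvement, low severity)

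*Protocol article*

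**What the plan says.** The rule stands in the Protocol article under Feasibility: Attrition and Adherence, after the definitions of completers, dropouts and noncompleters. Participants judged at risk by the research team are covered by this clause: "eg, psychologically), they may also be withdrawn from the study". It is permissive, names no criterion, and does not limit the withdrawal to treatment.

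The parts of the plan that it touches are these:

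- **In-treatment scores** (Weeks 1 to 10): "During the intervention period, we will send participants biweekly questionnaires".
- **Post-treatment assessment** (Week 10 to 11): "Once the intervention is complete, participants repeat the questionnaires and the reactivity testing paradigm from week zero to provide a second measurement".
- **Follow-up** (Week 22): "Twelve weeks after their final visit, we will follow up with the participants on all baseline questionnaires".
- **Retest condition** (Objective Measures): the repeat reactivity test is limited to people with 7 to 10 sessions. No such limit is placed on questionnaires.
- **Analysis** (Analyses for Rating Scales): a generalized mixed linear model compares the arms "using scores on DERS-16 across several time points (pre- and posttreatment as well as biweekly and bimonthly time points"), and Cohen d "or nonparametric tests will calculate the effect size between the 2 conditions".
- **Masking** (Randomization and Masking): on the assignments, "they will be kept hidden from researchers and research assistants until the participants begin the trial".
- **Safety contact in the control arm** (Calm Place as the Active Control): "The research team will contact these minimal-attention control participants weekly to check whether they use the application and to verify their safety".

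**The concern.** Stopping a treatment for safety and stopping outcome collection are separate decisions, and the clause as printed joins them. Clinicians must be free to stop therapy or VR exposure. That does not require giving up a later questionnaire from someone willing to complete it.

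The trigger is related to the outcome. A person judged psychologically at risk is likely to differ from the rest of the arm on the DERS-16, PHQ-9, GAD-7 or CORE. If the post-treatment scores of such people are missing, the scores that remain come from a selected and probably better-off group.

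The trial sets out to study benefits and challenges, to estimate between-group and within-group effect sizes, and to supply inputs for the power of a larger trial. The people removed for risk say a good deal about the challenges, and with 20 per arm each of them is 1/20 = 5% of an arm.

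**Working it through.** The plan gives no figure on this point: no expected number of at-risk withdrawals and no bias estimate. The check is therefore a reading of the text, a count of data points, and an illustration with assumed inputs.

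**1. What the clause ends.** Withdrawal from a study ordinarily ends its data collection, and no section provides for follow-up after such a withdrawal. The article does not state that questionnaires stop, so the loss is an inference from the ordinary meaning of the words.

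**2. Points kept per person.** Assume that biweekly means every two weeks, with scores at weeks 2, 4, 6 and 8 and the last one merged into week 10 to 11. The DERS-16 then has 7 points: weeks 0, 2, 4, 6, 8, 10–11 and 22. The bimonthly points have no stated schedule and are not counted.

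| Stopped in week | Withdrawn from the study: points kept | of which post-treatment | Intervention stopped, both later questionnaires given: points kept | of which post-treatment |
|---|---|---|---|---|
| 3 | 2 of 7 | 0 of 2 | 4 of 7 | 2 of 2 |
| 5 | 3 of 7 | 0 of 2 | 5 of 7 | 2 of 2 |
| 7 | 4 of 7 | 0 of 2 | 6 of 7 | 2 of 2 |
| 9 | 5 of 7 | 0 of 2 | 7 of 7 | 2 of 2 |

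If biweekly means twice a week, more in-treatment points are kept, but the post-treatment count under study withdrawal stays at 0 of 2.

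**3. What each analysis does with the loss.** The mixed model keeps the baseline and the scores given before withdrawal. It copes with the missing scores as far as those earlier scores explain why the person was withdrawn. It does not if the team acted on something they do not show, such as a disclosure in a session or on a weekly call. A Cohen d or a nonparametric test on observed post-treatment scores omits the person.

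**4. Illustrative size for an observed-score comparison.** Let *k* of 20 in one arm be missing, with a mean outcome *D* SD worse than the rest of that arm.

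- Mean of the full arm = mean of the rest, worsened by (*k*/20) × *D*.
- Bias in that arm's observed mean = (*k*/20) × *D*, in favour of that arm.

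Neither *k* nor *D* is in the documents. Type I error is two-sided at nominal .05, from a noncentral t with 20 versus 20 − *k* people and noncentrality (*k*/20)*D* / √(1/20 + 1/(20 − *k*)).

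| *k* | Bias, *D* = 0.5 to 1.5 | Type I error |
|---|---|---|
| 1 | 0.025 to 0.075 SD | .051 to .056 |
| 2 | 0.05 to 0.15 SD | .053 to .073 |
| 4 | 0.10 to 0.30 SD | .060 to .140 |

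For scale, the standard error of a standardised difference with 20 per arm is about √(2/20) = 0.32.

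If both arms lose the same *k* with the same *D*, the bias in the difference is (*k*/20)*D* − (*k*/20)*D* = 0. Each within-arm change would still look better by (*k*/20)*D*.

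**The case against.** The strongest reply is that the harm is inferred. The clause does not say that questionnaires stop, it sits among treatment-status definitions where study and treatment language are mixed, and a condensed article may leave post-withdrawal follow-up to the full protocol. Part of this stands: the consequence is an inference, and the full protocol may provide for follow-up. But the point does not rest on silence. The article prints a rule and names the study as what the person leaves.

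Three stronger readings are tempting, and the documents do not support them.

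- **That the schedule itself shuts out anyone who stops early.** The wording on completing the intervention and on the final visit may suggest this. But both assessments carry fixed week headings (10 to 11, and 22), and the 7-session condition covers only the reactivity test.
- **That a team aware of the arm will withdraw people unevenly.** The team does know the arm once participation begins, but nothing shows imbalance, and Calm Place participants also have a weekly safety contact.
- **That withdrawn people vanish from the primary analysis.** Nothing says that their earlier DERS-16 scores are discarded, and the mixed model can use them.

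It is also fair to say that the clause is a discretionary safety provision for a vulnerable group, that safety withdrawals are themselves feasibility data, and that some of these people would remain missing even with the fix. All of this lowers the severity. None of it is a reason to join the two kinds of stopping in one rule.

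**Conclusion.** The point holds as a modest one. The printed rule, in its ordinary meaning, gives up post-treatment outcomes from people whose risk status is related to those outcomes, and the planned analyses recover that only in part. The actual size cannot be stated. In the illustration it is small for one or two people (at most 0.15 SD, against a standard error of about 0.32), and it becomes material only at around four in one arm.

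Those figures assume withdrawals in one arm only, an analysis of observed post-treatment scores, and the chosen values of *D*. The mixed model would show less bias where earlier scores reflect the risk.

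This is a cheap improvement of low severity. It does not show that the trial's comparison is biased.

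**What to change.** Under Feasibility: Attrition and Adherence:

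- State that participants judged at risk may be *discontinued from the intervention*, in place of withdrawal from the study.
- Keep collecting the already planned week 10 to 11 and week 22 questionnaires from those who agree and where contact is clinically appropriate. Time both from week 0, so that an early last visit does not move them.
- Leave out the VR height test for these people.
- Report team-initiated safety discontinuations by arm, using the reasons for dropping out that the section already plans to record where possible.

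The cost is one wording change with an ethics-board amendment, a little more follow-up work with people who have stopped treatment, and a clinical judgement before each contact. No new instrument is needed, and clinicians keep full freedom to stop treatment.
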